## 8.2 STRC SAE Reporting Requirements

The Safety and Toxicity Review Committee (STRC) is responsible for reviewing SAEs for CCCWFU Institutional studies as outlined in Appendix B. STRC currently requires that all unexpected grade 4 and all grade 5 SAEs on these trials be reported to them for review. This procedure is a part of the CCCWFU Data Safety Monitoring Plan that our institution has on file at the NCI. All CRM staff members assisting a PI in investigating, documenting and reporting an SAE qualifying for STRC reporting are responsible for informing a clinical member of the STRC committee as well as the entire committee via the email notification procedure of the occurrence of an SAE.

## 8.3 WFUHS IRB AE Reporting Requirements

Any unanticipated problems involving risks to subjects or others and adverse events shall be promptly reported to the IRB, according to institutional policy. Reporting to the IRB is required regardless of the funding source, study sponsor, or whether the event involves an investigational or marketed drug, biologic or device. Reportable events are not limited to physical injury, but include psychological, economic and social harm. Reportable events may arise as a result of drugs, biological agents, devices, procedures or other interventions, or as a result of questionnaires, surveys, observations or other interactions with research subjects.

All members of the research team are responsible for the appropriate reporting to the IRB and other applicable parties of unanticipated problems involving risk to subjects or others. The Principal Investigator, however, is ultimately responsible for ensuring the prompt reporting of unanticipated problems involving risk to subjects or others to the IRB. The Principal Investigator is also responsible for ensuring that all reported unanticipated risks to subjects and others which they receive are reviewed to determine whether the report represents a change in the risks and/or benefits to study participants, and whether any changes in the informed consent, protocol or other study-related documents are required.

Any unanticipated problems involving risks to subjects or others occurring at a site where the study has been approved by the WFUHS IRB (internal events) must be reported to the WFUHS IRB within 7 calendar days of the investigator or other members of the study team becoming aware of the event.

Any unanticipated problems involving risks to subjects or others occurring at another site conducting the same study that has been approved by the WFUHS IRB (external events) must be reported to the WFUHS IRB within 7 calendar days of the investigator or other members of the study team becoming aware of the event.

Any event, incident, experience, or outcome that alters the risk versus potential benefit of the research and as a result warrants a substantive change in the research protocol or informed consent process/document in order to insure the safety, rights or welfare of research subjects.

# 9.0 STATISTICAL CONSIDERATIONS

This is a pilot study with the primary goal to be able to determine initial estimates of response rate (RR), and secondary goals to determine progression-free survival (PFS) and overall survival (OS). Data from this trial will also provide additional data concerning the safety profile of the CPI-613 therapy. We now describe anticipated accrual rates, proposed analyses, and sample size considerations.

Accrual Rate

We anticipate accruing one to two patients per month for this protocol. Thus, we anticipate that we will reach the target sample size of 20 patients treated at MTD within eighteen months.

Proposed Analyses

The analyses for this protocol will be primarily descriptive. With a sample size of 20 treated at MTD, we will be able to get initial estimates of RR, PFS, OS, and safety and toxicity.

For the primary outcome of tumor response rate we will present the proportion of patients who are CR, PR, SD or PD (Complete response, Partial response, stable disease and progressive disease, respectively). In addition, we will estimate the proportion of responders as the percent of patients who are SD, PR and CR, as well as RR (sum of PR + CR) and Disease Control Rate (DCR, which is the sum of SD, PR and CR). For these rates we will also include 95% confidence intervals.

For the time-to-event outcomes, we will estimate survival curves for OS and PFS using Kaplan-Meier techniques. In addition, we will estimate the 6 month and 1-year OS and PFS rates for these participants. We will estimate median overall and progression free survivals for these patients as well. We will also examine safety and toxicities for these 20 patients by looking at each toxicity identified earlier in the protocol by grade.

Sample Size Considerations

Since this is a single arm pilot study, our primary goal is to gather preliminary data on response rates and not to test a specific hypothesis per se. With this sample size we will be able to estimate the response rate using a 2-sided 95% confidence interval with an interval that will extend no more than 0.21 from the observed response rate (if we conservatively assume a response rate of 0.5 for calculations).

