# 1.0 BACKGROUND AND STUDY OBJECTIVES

## 1.1 Small Cell Lung Carcinoma

SCLC accounts for ~15% of all lung cancers. SCLC is a common lung malignancy caused by tobacco smoking. There are ~30,000 cases in the US each year. Two-thirds of patients present with extensive stage disease at the time of diagnosis. In patients with extensive stage disease, chemotherapy with a traditional platinum doublet can achieve response rates of up to 80% and improve survival. However, there are few durable responses, and in the majority of these patients, disease eventually returns. Most patients relapse with relatively resistant disease and have a median survival of only 4 to 5 months, and have increased morbidity. Current guidelines from the National Comprehensive Cancer Network (NCCN) recommend clinical trials for patients with recurrent disease (http://www.nccn.org/index.asp).

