# 3.0 PATIENT ELIGIBILITY CRITERIA

## 3.1 Inclusion Criteria

Patients must meet all of the following inclusion criteria before enrollment:

A. Histologically or cytologically proven SCLC that has relapsed or been refractory after at least one line of chemotherapy.

B. ECOG Performance Status of ≤2.

C. Must be ≥18 years of age.

D. Expected survival >1 month.

E. No acute toxicities from previous treatment higher than grade 1 at the start of treatment with CPI-613.

F. Women of child-bearing potential (i.e., women who are pre-menopausal or not surgically sterile) must use accepted contraceptive methods (abstinence, intrauterine device [IUD], oral contraceptive or double barrier device) during the study, and must have a negative serum or urine pregnancy test within 1 week prior to treatment initiation.

G. Men must practice effective contraceptive methods during the study, unless documentation of infertility exists.

H. Laboratory values ≤2 weeks prior to registration must be:

- platelet count ≥100,000 cells/mm^3^ or ≥100 bil/L
- absolute neutrophil count [ANC] ≥1500 cells/mm^3^ or ≥1.5 bil/L
- aspartate aminotransferase [AST/SGOT] ≤3x upper normal limit [UNL]
- bilirubin ≤1.5x UNL
- serum creatinine ≤1.5 mg/dL or 133 µmol/L
- albumin >3.0 g/dL or >30 g/L.

I. Mentally competent, ability to understand and willingness to sign an IRB-approved written informed consent form.

J Have access via central line (e.g., portacath) – double lumen due to CPI-613 administration requirements

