| * Cycle Length is 4 weeks, with treatment on Days 1 and 4 of Weeks 1 through 3; week 4 is a rest  week (no treatment)  ** The only pre-study data that will be used for data analyses are ECOG status, baseline CT or PET/CT, and LDH. See section 5.1.4 for details.  a: Pre-study requirements must be completed **within** **the following time**  **frames:**  Within **4** weeks: tumor assessments based on contrast CT of chest and abdomen or PET/CT;  Within **2** weeks: medical history, physical exam, vital signs, height, weight, ECOG, evaluation of symptoms and medications, clinical chemistry, hematology, LDH  Within **1** week: pregnancy test for women of childbearing potential  b: Specific chemistries are listed in section 5.2.2. Renal function will be assessed using the Cockcroft-Gault formula.  c: Serum pregnancy test for women of childbearing potential  d: These tests are performed with results available for review within 24 hours before administration of CPI-613  e: CPI-613 is given as a 2-hr IV infusion via a central venous catheter. Treatment with CPI-613 may be adjusted +/- 1 day.  f: Imaging performed while on treatment should be preferably obtained on day 3, 4, or 5 of week 4 during cycles 2, 4,  6 and every two cycles thereafter until progression.  g: Survival and post-study cancer treatment will be monitored bimonthly via telephone contact by the study PA after  patients are taken off of the trial. Phone contact will continue indefinitely.  h: Physical exam and clinical evaluation to be completed within 72 hours prior to treatment with CPI-613 | | | | | | | | | |

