### 5.1.3 Tumor Assessment

Tumor response will be assessed based on RR, and PFS, derived from contrast CT of chest and abdomen and/or PET/CT at baseline and after every two cycles. Contrast CT and/or PET/CT should be performed during week 4, preferably on Wednesday or later (days 3, 4 or 5). RR is the primary endpoint, whereas PFS and OS are secondary endpoints.

According to the Response Evaluation Criteria in Solid Tumors (RECIST), the efficacy of treatment for solid tumors is determined by the tumor size. RECIST criteria are the golden standard to evaluate the tumor. In this study RECIST criteria will be used to evaluate response. However, there is a *pseudoprogression* phenomenon described with the use of CPI-613 in Phase I solid tumor studies (Lee et al. 2012).

It is felt that if CPI-613-induces necrosis of the tumor lesion there may be some radiographic evidence for increasing size. CPI-613 induces tumor necrosis due to its mechanism of action – selectively targeting the altered form of mitochondrial energy metabolism in tumor cells, causing changes in mitochondrial enzyme activities and redox status, which leads to apoptosis, necrosis, and autophagy of tumor cells (Lee et al., 2011; Lee et al., 2012; Senzer et al., 2012; Zachar et al., 2011; Retter et al., 2012).

For the purposes of this study, pseudoprogression will be defined and considered in patients who meet RECIST criteria of progression. It will be the treating physician’s discretion to continue treatment in this situation if the patience is deemed to be getting clinical palliative benefit. In these patients, the study drug can be given for another two cycles prior to making definitive determination of progression or response.

OS will be determined from the first dose of CPI-613 to death, assessed until patient death..Post-study survival, medical and cancer treatment information will be collected bimonthly via telephone contact after treatment termination.

RR is defined as % of patients who experienced a complete response (CR) or partial response (PR). CR and PR are based on Response Evaluation Criteria in Solid Tumor (RECIST) Version 1.1 (Eisenhauer et al. 2009). The best response recorded from the start of the treatment until disease progression (DP) will be considered.

PFS will be determined from the first dose of CPI-613 to DP or death due to any cause.

*5.1.4 Use of pre-study data for analyses*

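### Section 9 counts stable disease in its responder proportion, so that figure duplicates the DCR and conflicts with response defined as CR or PR

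*Protocol*

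**What the plan says.** RR is the primary endpoint. Section 5.1.3 (Tumor Assessment) defines it by RECIST 1.1: "RR is defined as % of patients who experienced a complete response (CR) or partial response (PR". It adds the window for best response: "The best response recorded from the start of the treatment until disease progression (DP) will be considered".

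Section 9.0 (Statistical Considerations, Proposed Analyses) covers the primary outcome in one paragraph with three steps:

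- The categories: "we will present the proportion of patients who are CR, PR, SD or PD".
- A responder proportion: "we will estimate the proportion of responders as the percent of patients who are SD, PR and CR".
- In the same sentence, two named rates: "as well as RR (sum of PR + CR) and Disease Control Rate (DCR, which is the sum of SD, PR and CR".

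The paragraph closes by giving these rates 95% confidence intervals. Section 9.0 describes the study as a pilot with mainly descriptive analyses, 20 patients treated at the MTD and no formal hypothesis.

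**The concern.** The sentence names three measures but defines only two. The responder proportion and the DCR have the same numerator, while RR leaves out stable disease. A patient whose best response is SD is therefore a responder under one clause of Section 9.0 and a non-responder under the next clause and under Section 5.1.3. The Schema also lists response and stable disease as separate outcomes.

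In a single-arm, open-label pilot the estimate is the whole result. If the responder proportion is quoted from the primary-outcome analysis with its confidence interval, readers will take it for an objective response rate when it is a disease control rate. An unseen SAP would not remove this, because the conflicting definition stands in the protocol itself.

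**Working it through.** **Definitions side by side.** Let c, p and s be the numbers of patients with best response CR, PR and SD, and N the number of patients (20, Section 6.1 and Section 9.0).

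| Term | Place | Formula |
| --- | --- | --- |
| RR | Section 5.1.3 | (c + p)/N |
| RR | Section 9.0 | (p + c)/N |
| Responders | Section 9.0 | (s + p + c)/N |
| DCR | Section 9.0 | (s + p + c)/N |

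- The two RR definitions agree.
- Responders minus DCR = 0 for any data.
- Responders minus RR = s/N. With N = 20, each SD patient adds 1/20 = 5 percentage points.

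**Illustration.** The protocol gives no expected counts, so these are assumed: c + p = 2, s = 6, N = 20. The protocol does not name an interval method; Clopper-Pearson is used here.

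- RR = 2/20 = 10% (95% CI 1.2% to 31.7%).
- Responders as worded = (6 + 2)/20 = 8/20 = 40% (19.1% to 63.9%), identical to DCR.
- Difference = 6/20 = 30 percentage points, all of it stable disease.

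**Patients without a post-baseline scan.** This check bears only on the clarification of the denominator.

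- The first on-treatment scan is in week 4 of cycle 2. Section 5.0 says: "Imaging performed while on treatment should be preferably obtained on day 3, 4, or 5 of week 4 during cycles 2, 4". Cycle 1 is 28 days and the first three weeks of cycle 2 are 21, so the preferred days are 28 + 21 + 3 = 52 to 28 + 21 + 5 = 54.
- Section 1.1 says that most relapsed patients "have a median survival of only 4 to 5 months". Section 3.1 requires "Expected survival >1 month".
- Assume exponential survival from the first dose with median m months. Then P(death by day d) = 1 − 2^(−t/m), with t = d/30.44. Day 52 is 1.71 months and day 54 is 1.77 months.
- m = 4: 0.256 to 0.265. m = 5: 0.211 to 0.218. Times 20, that is 4.2 to 5.3 patients.
- Now assume instead that nobody dies in month 1 and the same hazard applies afterwards. Then t falls by 1, to 0.71 and 0.77 months. The result runs from 0.09 (m = 5, day 52) to 0.13 (m = 4, day 54), or about 2 of 20.

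Death before the first scan is thus plausibly 9% to 26%, depending on an assumption that the protocol does not settle.

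**The case against.** The strongest reply is that the primary endpoint is untouched. RR is named as primary throughout, defined as CR or PR in Section 5.1.3, and repeated correctly in the disputed sentence. The SD-inclusive figure is introduced as an addition, and CR, PR, SD and PD are each reported, so a careful reader can separate stable disease from response. There is no hypothesis test, stopping rule or go/no-go threshold that the figure could tip. All of this stands, and it limits the severity. It does not excuse the label: the figure sits in the primary-outcome paragraph, gets a confidence interval and is called a responder proportion while stable disease is not response anywhere else.

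Two stronger readings are tempting, and the documents support neither.

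- **That the four categories will drop early deaths and inflate the rate.** If 5 of 20 were left out, the illustrative RR would go from 2/20 = 10% to 2/15 = 13.3%. But Section 5.1.3 defines RR as a percentage of patients and Section 9.0 speaks of 20 treated, which reads most naturally as all treated patients, with an unscanned death a non-responder. Nothing restricts the denominator to scanned patients, and rules for non-evaluable patients are commonly left to a SAP. At most, the four categories may not add up to 20.
- **That the stated precision of 0.21 fails once unscanned patients are removed.** The protocol states that figure for its sample size of 20. It never gives a smaller denominator, so a half-width worked out on one shows no error in the plan.

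**Conclusion.** The point holds as a conflicting definition within the primary-outcome paragraph. The responder proportion equals DCR for every possible dataset and exceeds RR by the full SD proportion, s/20. That identity needs no assumption. The 30-point gap in the illustration does depend on the assumed counts of 2 CR/PR and 6 SD.

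A reader might infer that the primary endpoint has been redefined to include stable disease. It has not: RR as CR or PR is stated correctly in both sections. The error should be corrected because it invites a misleading headline, but it does not invalidate the primary analysis. The handling of patients without a post-baseline scan is a minor clarification and not an error in itself.

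**What to change.** In Section 9.0, strike the clause that defines responders to include SD, so that the sentence estimates RR (CR or PR) and DCR (SD, PR or CR), each with its 95% confidence interval. Use responder only for CR or PR, as in Section 5.1.3, and report SD+PR+CR only under the name DCR.

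As a clarification, add one sentence: RR and DCR use all treated patients as the denominator, and a patient with no post-baseline scan counts as a non-responder.

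The cost is a small wording amendment. Treatment, visits, data collection and sample size do not change. The figure reported as the responder proportion will be lower by the SD proportion, and the same information remains available as DCR.

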## 6.2 Adverse Event-Related Dosing Delay and Dose Modification

For adverse events unrelated to serum creatinine elevation or reduction in renal function but are possibly related to CPI-613, the occurrence of Grade 1 toxicity does not generally require dose modification for subsequent doses for that patient. However, if Grade 2 toxicity (other than alopecia and nausea) probably related to CPI-613 develops, treatment is to be withheld and can resume only after the Grade 2 toxicity has been reduced to Grade 1 or below, and the dose level for subsequent doses for that patient will be reduced by 25% of the dose at which such Grade 2 toxicity occurs. Grade 2 alopecia and nausea do not require withholding treatment or dose reduction. If Grade 3 or 4 toxicity probably related to CPI-613 develops, dosing of CPI-613 of that patient will be withheld and the patient shall be monitored for recovery from, and reversibility of, such Grade 3 or 4 toxicity. To resume treatment with CPI-613 for a patient who has had CPI-613-related Grade 3 or 4 toxicity, the Grade 3 or 4 toxicity must be reduced to Grade 1 or below, and the dose level for subsequent doses for that patient will be reduced to 50% of the dose at which such Grade 3 or 4 toxicity occurs.

For adverse events related to creatinine elevation or reduction in renal function that are possibly related to CPI-613, dosing of the patient will be withheld if the severity level is Grade 1 or above. Treatment can resume only after the toxicity has been reduced to Grade 0. The dose level for subsequent doses for that patient will be reduced by 15% if the severity level is of Grade 1, by 25% for Grade 2 toxicity, and by 50% for Grade 3 or 4 toxicity.

Furthermore, if the toxicity possibly related to CPI-613 is acute renal failure and the severity level is Grade 3 or 4, further patient enrollment will be temporarily suspended in order to enable assessment of the following aspects of the trial and implementation of corrective measures or protocol amendment, and if necessary:

- compliance of the study sites and investigators to the study protocol

- evaluation of the appropriateness of the procedures for monitoring renal function

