## 7.2 Handling of CPI-613

CPI-613 is an investigational drug and its toxicity in humans is not fully understood. All necessary precautions in handling potentially toxic chemicals must be strictly adhered to. Gloves and protective clothing must be worn when handling CPI-613. Avoid contact by all modes of exposure. If the solution contacts the skin, it must be washed immediately and thoroughly with soap and water. If the solution comes in contact with mucous membranes, the membranes must be flushed thoroughly with water. Spills should be picked up with absorbent material and the area must be washed at least 3 times with ethyl alcohol followed by water.

CPI-613 drug product is slightly photosensitive (Study# PHO-001). Therefore, after removal of CPI-613 drug product from the amber vials, CPI-613 drug product should be protected from excessive light before administration to patients.

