**List of Adverse Events to be Reported:**

*Abdominal pain

*Alkaline phosphatase

*ALT (SGPT)

*Anorexia

*AST (SGOT)

*Bilirubin (hyperbilirubinemia)

*Calcium (hypercalcemia, hypocalcemia)

*Creatinine

*Diarrhea

*Flushing

*Hemoglobin (anemia)

*Injection site Reaction

*Leukocytes

*Lymphopenia

*Nausea

*Neutrophils (neutropenia)

*Platelets (thrombocytopenia)

*Potassium

*Sodium

*Vomiting

All adverse events should be reported in the AE reporting log (Appendix C) and in ORIS regardless of whether they are on this list. Asterisk (*) denotes expected Adverse Events.

All Serious Adverse Events (SAEs) which are Possibly, Probably or Definitively Related to CPI-613, and Unexpected are required to be reported to Cornerstone Pharmaceuticals via the provided SAE Reporting Form within 7 days. All completed forms must be sent to [name] at Cornerstone. Cornerstone will submit any applicable SAEs to the FDA.

SAE reports must be submitted to Cornerstone by fax or email to the following address:

Department of Regulatory and Clinical Affairs

Cornerstone Pharmaceuticals, Inc.

[name]

[name]

[contact]

Telefax: [contact]

Email: [[contact]](mailto:[contact])

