# APPENDIX C – CCCWFU ADVERSE EVENT LOG

# *Only Grade 3 OR higher Need to be recorded*

# APPENDIX D – Data Collection Form for Efficacy Assessment

**ORIS PID:** _______________________ **Date Completed:** ____ / ____ / ____

**Visit:**  Pre-study  Cycle 1 Visit  Cycle 2 Visit  Cycle 3 Visit  Cycle 4 Visit

Cycle 5 Visit  Cycle 6 Visit  Cycle 7 Visit  Cycle 8 Visit  Cycle 9 Visit

Cycle 10 Visit  Other (Specify: _________________________________)

**ECOG Performance Status (Date Performed:** ____ / ____ / ____)

0 Fully active, able to carry on all pre-disease performance without restriction.

1 Restricted in physically strenuous activity but ambulatory and able to carry out work of a light or sedentary nature, e.g., light house work, office work.

2 Ambulatory and capable of all self-care but unable to carry out any work activities. Up and about more than 50% of waking hours.

3 Capable of only limited self-care. Confined to bed or chair more than 50% of waking hours.

4 Completely disabled. Cannot carry on any self-care. Totally confined to bed or chair.

**Date of contrast CT (chest / abdomen) and/or PET/CT**: ____ / ____ / ____

**Were new lesions identified on contrast CT (chest / abdomen) and/or PET/CT?**  Yes  No

**Has this subject progressed according to RECIST criteria? (As determined by the treating physician)**  Yes  No

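### Section 9 ties the toxicity summary to toxicities the protocol already names, so an unforeseen adverse event has no planned row; Section 8.1 and Appendix C also conflict on which events are recorded

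*Protocol*

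**What the plan says.** Section 2.2 of the protocol names safety and toxicity among the secondary outcome measures. Section 9.0 (Proposed Analyses) describes in one sentence how they will be summarised for the 20 patients: by "looking at each toxicity identified earlier in the protocol by grade".

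The only adverse event list before Section 9 follows Section 8.1 under the title "List of Adverse Events to be Reported". It has 20 terms, each with an asterisk, and the key reads "Asterisk (*) denotes expected Adverse Events". The same section sets a wider rule for data collection: "All adverse events should be reported in the AE reporting log (Appendix C) and in ORIS regardless of whether they are on this list".

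The log in Appendix C carries a different instruction: "Only Grade 3 OR higher Need to be recorded".

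Section 6.2 mentions two toxicities that are not on the list. One is alopecia ("Grade 2 alopecia and nausea do not require withholding treatment or dose reduction"). The other is acute renal failure, which at Grade 3 or 4 triggers a pause in enrolment. On how much is known about the drug, Section 7.2 says: "CPI-613 is an investigational drug and its toxicity in humans is not fully understood".

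**The concern.** Collection is open-ended, while the analysis as described is closed. If the rows of the toxicity table are fixed by what the protocol already names, the table can refine what is known about anticipated toxicities but cannot show a new one. Section 9 says the trial will contribute further safety data, and for a drug at this stage an unanticipated event is among the most informative findings such a study can yield. A team that followed the sentence literally would hold those events in its database and omit them from the summary of a declared secondary outcome.

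The conflict over recording makes this worse. If staff follow the instruction on the log rather than Section 8.1, Grade 1 and 2 events may never be entered. The by-grade summary would then be incomplete for listed and unlisted terms alike.

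**Working it through.** Section 9 states no figure for safety, so there is none to reproduce. The check compares the scope of the analysis with the scope of the data, then illustrates the size of the gap.

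**Step 1: what the analysis sentence covers.**
- Terms in the Section 8.1 list: 20.
- Terms with the asterisk for expected: 20 of 20, so no listed term is marked otherwise.
- Toxicities named before Section 9 but not listed: at least two, alopecia and acute renal failure (Section 6.2). The list has creatinine but not renal failure.

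On the narrow reading the table has 20 rows. On the wider reading it gains the few toxicities named elsewhere. On neither reading does it include an event the protocol did not mention.

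**Step 2: what is collected.** Section 8.1 puts all adverse events in scope, with no grade limit. The laboratory panel in Section 5.2.2 also goes beyond the list. Magnesium, albumin and glucose are measured, and Table 5-1 schedules chemistry on Day 1 of Weeks 1 to 3, but the list has no term for an abnormality in any of the three.

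**Step 3: whether by-grade data will exist.**

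| Source | Events to record |
| --- | --- |
| Section 8.1 | All adverse events, listed or not, any grade |
| Appendix C log | Grade 3 or higher |

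Both rules govern the same log, and they cannot both be followed. Section 6.2 also acts on Grade 1 renal events and on certain Grade 2 events, so the lower grades matter to the conduct of the trial as well as to its report.

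**Step 4: illustration of size.** The protocol gives no incidence for any unlisted toxicity, so the true rate p is assumed. With n = 20 (Section 6.1), the chance of at least one case is 1 − (1 − p)^20:
- p = 5%: 1 − 0.95^20 = 0.642, or 64%
- p = 10%: 1 − 0.90^20 = 0.878, or 88%
- p = 20%: 1 − 0.80^20 = 0.988, or 99%

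An unlisted toxicity of moderate frequency would thus probably be seen in this trial and would still have no planned row.

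**The case against.** The strongest reply is that this is one loosely worded sentence in a descriptive pilot. It does not say that only named toxicities count. Section 9 also promises initial estimates of safety and toxicity without limiting them to a list, and adverse event tables are usually specified in a statistical analysis plan, which was not available here. Serious novel events also have other routes: the sponsor, the Safety and Toxicity Review Committee and the IRB.

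Part of this stands. The exclusion is inferred from the only method described; it is not stated. But that method is a selection rule, and an analysis plan that followed it would inherit the restriction. Expedited reporting is case-by-case oversight. It yields no incidence by grade, and the committee's table in Appendix B does not require Grade 1 to 3 events at all.

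A reader might infer more than the documents support:
- *All unexpected events fall outside the table.* Unlisted is not the same as unexpected. Section 8.1 confines expectedness to expedited reporting, and the Appendix B form treats severity as well as nature as possible grounds for calling an event unexpected. A listed term can therefore be unexpected and still be tabulated. Alopecia and acute renal failure carry no asterisk, yet arguably count as identified earlier.
- *Every unlisted event is at least recorded.* Appendix C contradicts this for Grades 1 and 2.
- *A missing row would be read as 0 of 20, with an exact 95% upper limit of 16.8%.* Nothing in the protocol suggests that an absent row would be presented or read as zero.

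**Conclusion.** The point holds as a mismatch of scope. The toxicity summary is tied to pre-named terms, essentially the 20 expected ones plus at most a few from elsewhere in the protocol, while Section 8.1 calls for all adverse events. Read as written, the plan has no row for an unforeseen toxicity. Separately, Section 8.1 and Appendix C contradict each other on which grades are recorded, and that contradiction does not depend on how Section 9 is read.

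The primary outcome is unaffected, and the authors may well have intended a full table. The change should still be made, because the sentence as it stands permits a safety summary that omits new findings. The 64%, 88% and 99% probabilities rest on assumed rates and show only that the gap could matter in 20 patients; they do not predict what will occur.

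**What to change.** 1. In Section 9, replace the phrase that limits the summary to previously identified toxicities with wording such as: *all recorded adverse events, from first dose until one month after last dose, by CTCAE term and worst grade per patient, in all treated patients, with terms listed in Section 8.1 and unlisted terms shown separately*. The time window is the one already set in Section 5.1.2, and the 20 listed terms remain as a subset.
2. Reconcile Section 8.1 with the instruction on the Appendix C log so that one recording rule applies. Without this, the by-grade table cannot be complete even after the first change.

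The cost is one amended sentence, a longer table and one aligned form instruction. If Grade 1 and 2 events are recorded as Section 8.1 says, there will also be some added log entries. No extra patients or tests are needed.
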